## Abstract

**Background:**

Behavioral activation (BA) is an effective and efficacious treatment for depression. Activity scheduling is the central treatment component of BA and involves planning of potentially enjoyable and rewarding activities. Evidence from non-clinical studies suggests that mental imagery simulations of planned activities can increase motivation and anticipated pleasure for these activities.

**Method:**

We describe a randomized controlled trial testing a mental imagery activity scheduling training delivered online in four weekly sessions (total training duration approximately 90 minutes) in a sample meeting diagnostic criteria of a major depressive episode, as indicated by the Diagnostic Short-Interview for Mental Disorders (Mini-DIPS), and not currently receiving treatment. Participants (N = 140) will be randomized to either mental imagery activity scheduling or a wait-list control condition. Depressive symptoms (BDI-II) and behavioral activation (BADS) are the primary outcomes; BDI-II will be measured at Session 1, Session 4, and at two-week follow-up, BADS at Sessions 1-4 and at two-week follow-up.

**Discussion:**

It is discussed how the expected results may reflect mechanisms and effects of a mental imagery activity scheduling training delivered online in a sample of individuals with depression. Concluding we outline next steps for future research and highlight the potential of this novel treatment for dissemination in the wider community and integration into routine care.

A deficit in reward processing is one of the core clinical features of major depressive disorder (MDD). According to early behavioral models, MDD is associated with a decreased engagement in potentially rewarding activities, which leads to reduced reward experiences and a worsening of mood (Lewinsohn, 1974). A number of studies support this theoretical account. Behavioral and neuroimaging findings have suggested that patients with MDD are hyposensitive to reward and hypersensitive to punishment (Alloy et al., 2016; Eshel & Roiser, 2010). In addition, compared to healthy controls, patients with MDD show a reduced expectation of how rewarding or pleasant a future stimulus will be (Gorka et al., 2014). This phenomenon, also referred to as low anticipation of reward, has been related to less active behavior and less positive affect (Bakker et al., 2017).

One effective psychotherapy that aims to target these deficits in reward processing is behavioral activation (BA; Dimidjian et al., 2006, 2011; for a meta-analysis, see Cuijpers et al., 2023). BA can consist of different procedures, of which activity scheduling (i.e., scheduling activities with the aim to increase positive reinforcement) and skill training (i.e., such as social or problem-solving skills) have received most support (Kanter et al., 2010). Multiple studies on BA procedures have linked these interventions to increases in self-reported levels of behavioral activation and to decreases of depressive symptoms (Stein et al., 2021), and even suggested that behavioral activation may play a role across different types of psychotherapies (Bruijniks et al., 2022). Although research that links BA procedures or self-reported behavioral activation to changes in reward functioning is still scarce (Forbes, 2020; Janssen et al., 2021), some studies did already point to a positive association between reward anticipation and increased activation (Bakker et al., 2017; Dichter et al., 2009) and showed that procedures focused on behavioral activation seem to increase neural activity related to motivation (Mori et al., 2018). However, patients with MDD often suffer from low energy levels (Schuch et al., 2017) and poor motivation (Treadway & Zald, 2011) that can act as a barrier towards engaging in behaviors (i.e., activation) that might facilitate reward experiences. As there is still an urgent need to improve treatments for MDD (Cuijpers et al., 2021), identifying ways to optimize BA procedures to improve reward processing in patients with MDD might be a promising way forward.

Recent pre-clinical studies suggest that BA treatment might be facilitated by combining activity scheduling with mental imagery based procedures (Heise et al., 2022; Holmes et al., 2016; Renner et al., 2019). Mental imagery refers to the multi-sensory experience of information from memory (Kosslyn et al., 2001). Imagery-based procedures have a long tradition in many forms of psychotherapy. Prospective mental imagery involves the simulation of future situations or activities. In non-clinical samples, mental imagery of planned activities has been linked to increased motivation for engaging in these activities (Renner et al., 2019). Mental imagery of positive future events has also been shown to increase the estimated likelihood of future events (Boland et al., 2018) and to decrease depressive symptoms and perceived stress (Marciniak et al., 2024). Recently, we showed that affective mental imagery leads to higher motivation for completing activities compared to neutral mental imagery or no mental imagery, suggesting that an affective mental imagery component may be crucial to enhance motivation. These findings however did not translate to the actual performance of activities, possibly due to a ceiling effect within this non-clinical sample (Heise et al., 2022). In a sub-clinical sample, participants who were instructed to generate positive images showed better performance on a behavioral task compared to participants who were instructed to generate negative images (Pictet et al., 2011). Positive imagery has been shown to modulate early attention allocation towards stimuli associated with the imagined activities (Bär et al., 2023). In sum, these studies suggest that individuals with depression, who typically have lower activation levels compared to healthy controls (Manos et al., 2011; Pinto-Meza et al., 2006), might benefit from prospective mental imagery interventions. Indeed, a recent pilot randomized clinical trial that compared imagery-enhanced BA with a wait-list control condition in a sample of patients with late-life depression confirmed that adding mental imagery to BA is feasible and depressive symptoms decreased more in the imagery BA condition, including at 6-month follow-up (Pellas et al., 2022, 2023). However, in this trial the sample size was small (*N* = 41) and restricted to elderly patients with MDD.

While the effects observed by Pellas et al. (2022, 2023) are promising, there is a clear need for additional studies on the clinical utility of imagery-enhanced BA. Accordingly, we propose to test the effects of an unguided, online-delivered imagery BA intervention in a sample of individuals meeting diagnostic criteria for MDD. The change in study format from telephone-based, as in Pellas et al. (2022), to online-based facilitates easier dissemination, potentially expanding access to an empirically-supported treatment. Furthermore, we believe it is also highly relevant to investigate the role of individual differences for the effectiveness of imagery-enhanced BA. Research suggests that imagery vividness is reduced in persons experiencing symptoms of depression (Holmes et al., 2016). Since the intervention builds on imagery of planned, potentially rewarding activities we aim to investigate if individual differences in the ability to generate reward imagery moderate treatment effects. Likewise, some empirical data suggest that symptoms of anhedonia (Webb et al., 2023) and avoidance tendencies (Nasrin et al., 2017) might limit the effectiveness of BA. By investigating how imagery ability, anhedonia, and avoidance tendencies influence the effectiveness of the imagery-enhanced BA interventions we hope to gain a better understanding *for whom* this intervention works best, paving the way for treatment individualization in the future. Additionally, it may also shed some light on the mechanisms underpinning imagery BA effects, thus enabling potential increases in efficiency by focusing on the ‘active ingredients’.

The present study will test the acceptability, feasibility, and effects of a 4-session imagery BA intervention delivered over the internet on behavioral activation and depressive symptoms in individuals meeting diagnostic criteria for MDD. While results from several studies have already supported the use of BA in online settings (e.g., Mueller-Weinitschke et al., 2023; Potsch & Rief, 2024; Puspitasari et al., 2017; Weitzel et al., 2022), the presented study will be the first to test the acceptability, feasibility, and effects of an imagery-enhanced BA intervention in an online setting. Besides, the present study will include multiple measurements of potential mechanisms of change, thereby providing insights into the relationship between the procedure (imagery-enhanced activity scheduling), potential mechanisms of change (reward anticipation, motivation, and behavioral activation), and outcome (depressive symptoms). In addition, the present study will explore the moderating effects of imagery ability, anhedonia, and avoidance tendencies.

Specifically, we expect to find (1) an increase in behavioral activation, measured with the Behavioral Activation for Depression Scale (BADS; Kanter et al., 2007) weekly from baseline to Session 4 and at two-week follow-up, and (2) a decrease in depressive symptoms, measured with the Beck Depression Inventory-II (BDI-II; Beck et al., 1996) at baseline, Session 4, and at two-week follow-up, for participants in the Imagery BA condition, compared to participants in the wait-list control condition. We expect that this difference between conditions in behavioral activation and depressive symptoms will be present at the end of the intervention (Session 4) and will be maintained at two-week follow-up.

## Method

### Design

The study is a two-arm randomized controlled trial with one active intervention condition (Imagery BA) and one wait-list control condition. Participants in both conditions are invited to complete questionnaires at baseline (Session 1), Weeks 1-3 after baseline (Sessions 2-4) and at follow-up (Week 5 after baseline). The study has been pre-registered (see Heise et al., 2022S).

### Participants

Inclusion criteria are (a) meeting the diagnostic criteria for a current major depressive disorder (MDD) as indicated by the Diagnostic Short-Interview for Mental Disorders (Mini-DIPS; Margraf et al., 2017), (b) a BDI-II score ≥ 14, indicating at least mild levels of depression, and (c) age between 18 and 65 years. Participants will be excluded if (1) they are currently in treatment for a mental health condition (psychotherapy and/or medication), (2) they present high levels of suicidality (as indicated by answers > 1 for item 9 of the BDI-II or the respective section in the Mini-DIPS), or (3) if they are meeting diagnostic criteria for one or more of the following disorders: bipolar disorder, psychotic disorders, or substance dependence.

*Sample Size.* Our aim is to obtain a dataset containing *n* = 140 complete observations, that is, with measurements for all four sessions and follow-up. This sample size was pre-registered (Heise et al., 2022S) and determined a priori using GPower (Faul et al., 2009). We assumed a small effect size (as observed in initial pilot testing), 95% Power, and α = 0.05. To account for attrition as observed in initial pilot testing, in which approximately 26% of baseline participants did not complete the follow-up assessment, we plan to recruit a total of *N* = 192 participants from the general population.

### Procedure

#### Screening Process

To inform potential participants about the present study, advertisements and leaflets will be distributed through various online (social media groups, forums focusing on depression) and offline (general practitioners, psychotherapists, psychiatrists, outpatient clinics, university student counseling services) channels. Anyone interested in the study will be referred to an online screening website, where detailed information about the study’s procedures are provided and informed consent is obtained from interested potential participants. Next, participants complete the BDI-II and screening questions for the Mini-DIPS. If complying with inclusion and exclusion criteria, participants may book an appointment for a telephone interview by choosing a suitable date/time from a list displayed online.

#### Telephone Interview

In the telephone interview, trained interviewers complete the Mini-DIPS including sections on Major Depression and current suicidality as well as any other section identified through the respective screening question. This procedure allows assessing whether diagnostic criteria for inclusion/exclusion diagnoses are met as well as for any other diagnoses covered in the Mini-DIPS.

#### Measurements

Participants complete questionnaires at baseline, Weeks 1-3, and follow-up (Week 5; see Table 1 for a complete list of measures, forms, and sampling points) as part of the respective online sessions. Session invitations will be sent out via email. If participants fail to respond to a given session invitation by accessing the provided link within 24 hours, a reminder message is sent out. The link in the reminder message is valid for another five days; if this period elapses without response, the respective participant is excluded from further participation in the study.

**Table 1 t1:** Measures and Sampling Points

Measure	Screening	Session 1/ Baseline	Session 2	Session 3	Session 4	Follow-up
Primary outcomes						
BADS		x	x	x	x	x
BDI-II	x	x			x	x
Secondary outcomes						
Items on acceptability and feasibility						x
WEMWBS		x			x	x
Activity data						
Activity monitoring form		x		x	x	
Activity ratings			x	x		
Potential mediators (measured as activity ratings)						
Reward anticipation			x	x		
Motivation			x	x		
Potential moderators						
CBAS		x	x	x	x	
FRIS		x			x	
SUIS		x				
TEPS		x				

*Note.* BADS = Behavioral Activation for Depression Scale (Kanter et al., 2007); BDI-II = Beck Depression Inventory-II (Beck et al., 1996); CBAS = Cognitive Behavioral Avoidance Scale (Ottenbreit & Dobson, 2004); FRIS = Freiburg Reward Imagery Scale (https://osf.io/9y64q); SUIS = Spontaneous Use of Imagery Scale (Kosslyn et al., 1998); TEPS = Temporal Experience of Pleasure Scale (Gard et al., 2006); WEMWBS = Warwick-Edinburgh Mental Wellbeing Scales (Tennant et al., 2007).

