##### Depressive Symptoms

Depressive symptoms will be assessed at baseline (Session 1), Session 4, and at two-week follow-up using the Beck Depression Inventory-II (BDI-II; Beck et al., 1996). The BDI-II measures depressive symptom severity across 21 symptoms by letting respondents choose from four (for two symptoms, seven) statements (e.g., “I blame myself all the time for my faults.”) ranked by increasing severity (scoring 0-3 points per symptom). Total scores can range from 0 to 63, with 0-13 indicating minimal depression, 14-19 mild depression, 20-28 moderate depression, and 29-63 severe depression. Reliability and validity of the BDI-II are well supported (Kühner et al., 2007; Wang & Gorenstein, 2013).

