#### Secondary Outcomes

##### Acceptability and Feasibility

Acceptability and feasibility of the newly developed online imagery BA intervention tested in this study will be measured by dropout rate during the intervention and by a number of questions on acceptability and feasibility (e.g., “I liked the online format of the study”, “I found it difficult/unpleasant to engage with the study.”, “I would recommend the training to friends”). Responses will be recorded on seven-point Likert scales with end points labelled 0 “not at all” and 6 “very much” and will be obtained at follow-up or – in the case of drop-out – via an additional questionnaire sent to dropped-out participants. Furthermore, open-ended questions are included to encourage participant feedback on this newly developed intervention.

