##### Monitoring of Potential Adverse Effects

Potential adverse effects of the intervention will be assessed in terms of symptom deterioration (BDI-II) as well as through questions on acceptability and feasibility. To minimize the occurrence of adverse effects such as suicidal thoughts and behaviors, extra care is taken to identify persons at risk during the screening procedures and intake telephone interview (for details see inclusion criteria in the Participants section above). In addition, a safety protocol to deal with suicidal ideation that includes consultation with a clinical psychologist has been implemented.

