#### Hypothesis 2 – Depressive Symptoms

To test for differences between the Imagery BA condition and the wait-list control condition in change in depressive symptoms across the three measurement points (Session 1, Session 4, follow-up), we plan to conduct a repeated-measures ANOVA on the BDI-II score with condition (Imagery BA vs. wait-list control) as between-subject factor and time (Session 1, Session 4, follow-up) as within-subject factor in an intention-to-treat analysis.

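### Missing one session window ends all later BDI-II and BADS collection, so primary outcomes depend on session adherence and BDI-II worsening goes unseen in people who stop

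*Protocol article*

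**What the plan says.** The *Measurements* section of the protocol article states that questionnaires are completed "as part of the respective online sessions". A participant who has not opened the link after 24 hours gets a reminder: "The link in the reminder message is valid for another five days". If there is still no response by then, "the respective participant is excluded from further participation in the study". The rule is the same in both arms.

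On timing, the *Depressive Symptoms* section says: "Depressive symptoms will be assessed at baseline (Session 1), Session 4, and at two-week follow-up". Table 1 agrees: there is no BDI-II at Session 2 or 3. The BADS is taken at Sessions 1 to 4 and at follow-up.

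Both primary analyses (Hypotheses 1 and 2) are repeated-measures ANOVAs with time "as within-subject factor in an intention-to-treat analysis".

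On harms, *Monitoring of Potential Adverse Effects* states: "Potential adverse effects of the intervention will be assessed in terms of symptom deterioration (BDI-II". It then names the acceptability and feasibility questions as a second source. *Acceptability and Feasibility* says those questions are also put to people who drop out, "via an additional questionnaire sent to dropped-out participants". That questionnaire is not stated to contain the BDI-II or the BADS.

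*Study Format* adds that the study team follows progress and contacts participants where needed. No outcome collection after exclusion is described.

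**The concern.** The rule treats not attending a session and leaving the study as one event. A randomised person who misses one week but would answer at Week 5 is not asked. An intention-to-treat comparison needs outcomes from everyone randomised, whatever their adherence. Here adherence decides whether the outcome is sought. An analysis plan can model outcomes that were never requested, but it cannot restore them.

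The course content does not require this. Session 3 builds on activities scheduled in Session 2, which bears on the sessions but not on two questionnaires. In the wait-list arm the sessions contain only questionnaires.

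Three things are at stake:
- precision, because fewer randomised participants contribute post-baseline data;
- bias, if those who stop differ from those who stay and the arms lose people at different rates. The Imagery BA sessions last about 20 to 35 minutes and include tasks, so unequal loss is plausible, but no rates by arm are given;
- safety information, because worsening on the BDI-II is not measured in people who stop.

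**Working it through.** **1. The plan's own attrition figure.** Inputs from *Sample Size*: 140 complete observations, 26% without follow-up in the pilot, 192 to be recruited.
- 140 / (1 − 0.26) = 189.2, so 190, against 192 stated: reproduced to within two participants.
- 0.26 × 192 = 49.9, about 50 without follow-up; 192 − 50 = 142 with follow-up.

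**2. What each missed invitation removes** (*Measurements* and Table 1)

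| First missed | Not obtained through non-response | Not sought because of the rule |
|---|---|---|
| Session 2 | BADS at Session 2 | BADS at Sessions 3, 4 and follow-up; BDI-II at Session 4 and follow-up |
| Session 3 | BADS at Session 3 | BADS at Session 4 and follow-up; BDI-II at Session 4 and follow-up |
| Session 4 | BADS and BDI-II at Session 4 | BADS and BDI-II at follow-up |
| Follow-up | BADS and BDI-II at follow-up | nothing |

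The first three rows all leave no post-baseline BDI-II. The last row is unaffected by the rule.

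**3. How many fall in each row.** The documents do not give the timing of loss. Assume an equal proportion is lost at each of the four post-baseline invitations.
- Retention per invitation: q = 0.74^(1/4) = 0.9275, a loss of 7.3%.
- Excluded by Session 4: 192 × (1 − q³) = 38.8, about 39 (20%), with no post-baseline BDI-II.
- Lost at follow-up only: 192 × (q³ − q⁴) = 11.1, about 11.

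**4. What continued invitations could recover.** The share of the 39 who would answer at follow-up if asked is unknown. Follow-up data available out of 192:
- 0%: 142
- 25%: 142 + 0.25 × 39 ≈ 152
- 50%: 142 + 0.50 × 39 ≈ 162
- 75%: 142 + 0.75 × 39 ≈ 171

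**5. Possible bias in the BDI-II contrast.** Every input here is assumed: 33% dropout in the Imagery BA arm and 19% in the wait-list arm (mean 26% with equal arms), and dropouts in both arms scoring 5 points worse than those who stay.
- Observed Imagery BA mean too low by 0.33 × 5 = 1.65 points.
- Observed wait-list mean too low by 0.19 × 5 = 0.95 points.
- Bias in the contrast, in favour of Imagery BA: 1.65 − 0.95 = 0.70 points.
- Range over the assumed gap: 2 points gives 0.14 × 2 = 0.28; 8 points gives 0.14 × 8 = 1.12. With equal dropout and the same gap in both arms it is 0.

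The protocol calls its assumed effect small without a number. With d = 0.2 and SD 10 (both assumed), that effect is 2 points, so 0.70 is 35% of it. This is an upper-end figure because it attributes every loss to the rule.

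**The case against.** Much can be said for the plan.

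- **The window is not harsh.** It runs for about six days with a reminder, and the team may contact people. Many who ignore both messages would be lost anyway. This stands: the 26% is total pilot attrition, and a reader who took all 50 losses as the product of the rule would go beyond the documents.
- **Intention-to-treat is not contradicted.** The text excludes people from further participation, not from the analysis. Everyone randomised has baseline data and can be analysed in the assigned arm, and the handling of missing values may sit in an analysis plan not shown. A reader might infer a contradiction; the documents support only that the rule undermines the analysis by not seeking the data it needs.
- **BDI-II deterioration is not the only harm measure.** The acceptability questions use scales from 0 to 6, are named as a harm source and do reach dropouts, and there is a safety protocol for suicidal ideation. This stands, so harm in dropouts is not wholly unseen. The gap is specific to symptom worsening on the BDI-II.
- **The bias must be taken between arms.** Setting 1.65 points in one arm against a 2-point effect ignores wait-list dropouts, whose absence also makes their arm look better. The contrast is 0.70 on the same assumptions.
- **Unequal loss is conjecture.** Longer sessions may raise loss in the Imagery BA arm, and the offer of the intervention after follow-up may help retain the wait-list arm, but no arm-level rates are given.
- **A dropout rate needs some cut-off for non-response.** A prespecified cut-off is not itself a fault.

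None of these explains why the two primary questionnaires stop when a session is missed.

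**Conclusion.** The point holds as a design weakness stated in the protocol itself, not as detail left out of an article. Missing Session 2 or 3 ends all post-baseline BDI-II and later BADS collection, and missing Session 4 also ends follow-up. The rule turns a missed session into permanently missing primary outcomes, weakens the intention-to-treat comparison, and leaves BDI-II deterioration unmeasured in people who stop.

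The documents fix the mechanism but not its size. About 50 of 192 without follow-up is the plan's own expectation. About 39 with no post-baseline BDI-II rests on equal loss at each invitation, and the 0.7-point bias rests wholly on assumed rates, gap and SD. How many would have answered later is unknown. The case for change rests on the fact that outcomes not sought cannot be recovered after data collection ends, while seeking them is cheap.

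**What to change.** Limit the exclusion in *Measurements* so that it does not stop outcome collection:

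1. Keep sending the Session 4 and follow-up BDI-II and BADS, at their scheduled times, to every randomised participant in both arms who has not withdrawn consent.
2. Add the BDI-II and BADS to the questionnaire already sent to dropouts.
3. Report session discontinuation separately from missing assessments.

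Whether intervention sessions stay open after a missed one is for the sponsor and is not part of this change. The count of complete observations in the recruitment stop rule can keep its present definition (all four sessions and follow-up); the added outcomes serve the intention-to-treat analyses.

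The cost is a change to the survey-platform logic, a short amendment with matching consent wording, and a few more emails. Some outcomes will come from participants without full session exposure, which an intention-to-treat comparison is meant to include.
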